### Secondary outcome measurement

#### VAS for pain intensity

Pain intensity will be assessed using a 10-cm VAS. Participants will be asked to report the intensity of pain at weeks 0 (baseline), 1, 2, 3, and 7.

#### NDI

Neck pain-related disability will be evaluated using the validated Korean version of NDI. NDI is used to measure self-perceived disability caused by neck pain. It comprises ten items for pain intensity, concentration, functional activities, and headache [19]. Each question is assessed using a 6-point scale of 0–5, where 0 indicates the absence of a problem and 5 indicates severe disability caused by neck pain.

#### EQ-5D

The Korean version of the EQ-5D questionnaire will be used to measure the health-related quality of life of our patients with CNP. This questionnaire comprises five dimensions, including mobility, self-care, usual activities, pain/discomfort, and anxiety/depression [20]. Each dimension is rated on a scale of 1–3, where 1 indicates no problem and 3 indicates a major problem.

#### PGIC

At the end of each treatment session, the participants will complete the PGIC scale, which is a 7-point categorical scale. They will be asked to describe changes in activity limitations, symptoms, emotions, and overall quality of life. The PGIC scale is one of the most commonly used method of assessing clinically meaningful changes that make a difference to patients in studies on musculoskeletal conditions [21].

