**Methods:**

This seven-week clinical trial has been designed as an assessor-blinded, randomized controlled trial with three parallel arms. Thirty-six patients will be recruited and randomly allocated to three treatment groups: miniscalpel acupuncture treatment; NSAIDs; and miniscalpel acupuncture treatment combined with NSAIDs. Patients in the miniscalpel acupuncture and combined treatment groups will receive three sessions of miniscalpel acupuncture over a three-week period. Patients in the NSAIDs and combined treatment groups will receive zaltoprofen (one oral tablet, three times a day for three weeks). Primary and secondary outcomes will be measured at weeks 0 (baseline), 1, 2, 3 (primary end point), and 7 (four weeks after treatment completion) using the visual analogue scale and the Neck Disability Index, EuroQol 5-dimension questionnaire, and Patients’ Global Impression of Change scale, respectively. Adverse events will also be recorded.

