### Outcomes

The primary outcome will be measured using VAS. Changes in VAS scores after three weeks of treatment will be measured relative to the baseline scores and will be considered the primary outcome. The secondary outcome will be determined by the Neck Disability Index (NDI), EuroQol 5-dimension (EQ-5D) questionnaire, and Patient Global Impression of Change (PGIC) scale. Outcomes will be measured at weeks 0 (baseline), 1, 2, 3 (primary end point), and 7 (four weeks after treatment completion). Outcome measurements will be recorded by two independent researchers. Table 1 shows the treatment and outcome measurement schedules.

**Table 1 Tab1:** Treatment and outcome measurement schedules during our pilot study

Outcome measures	Screening	Week 0 (baseline)	Week 1	Week 2	Week 3	Week 7
Screening test	V					
Sociodemographic characteristics	V					
Randomization		V				
Laboratory test	V				V	
MA treatment		V	V	V		
NSAIDs prescription		V	V	V		
Visual analog scale	V	V	V	V	V	V
Neck Disability Index		V	V	V	V	V
EQ-5D questionnaire		V	V	V	V	V
PGIC scale			V	V	V	V
Adverse events		V	V	V	V	V
Credibility assessment					V	
Total safety assessment					V	

*NSAIDs* nonsteroidal anti-inflammatory drugs, *EQ-5D* EuroQol 5-dimension, *PGIC* Patient’s Global Impression of Change

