### Primary outcome measurement

VAS is a 10-cm measurement instrument to determine the severity of pain. A 10-cm horizontal line will be used. The individuals rate his or her pain on a scale of 0–10, where 0 indicates the absence of pain and 10 indicates the worst pain imaginable. Participants will estimate their level of pain by marking on the line. Then the distance from “absence of pain” point will be measured [17, 18]. In this study, the VAS score will indicate pain at the point of measurement. Changes in VAS scores after three weeks of treatment, relative to the baseline scores, will be considered the primary outcome.

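### The PGIC timing rule (end of each treatment session) conflicts with the visit schedule, does not fit the NSAIDs arm, and at weeks 1 and 2 makes the rating conditions differ between arms

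*Protocol article*

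**What the plan says.** The protocol article sets the timing of PGIC in three places.

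- **Secondary outcome measurement, PGIC:** "At the end of each treatment session, the participants will complete the PGIC scale". This ties the rating to a treatment event and places it after that event.
- **Outcomes, Table 1:** the PGIC row reads "PGIC scale V V V V", with the marks under weeks 1, 2, 3 and 7. The MA row reads "MA treatment V V V" and the drug row "NSAIDs prescription V V V", both with marks under weeks 0, 1 and 2. The PGIC row is not split by arm.
- **Outcomes, running text:** after naming PGIC among the secondary outcomes, it says "Outcomes will be measured at weeks 0 (baseline), 1, 2, 3 (primary end point), and 7 (four weeks after treatment completion". It makes no exception for PGIC.

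On what a session is, the Abstract (Methods) says "Patients in the miniscalpel acupuncture and combined treatment groups will receive three sessions of miniscalpel acupuncture over a three-week period". The NSAIDs arm takes oral tablets. Under Interventions, its visit contact consists of being given the prescription and handing back unused drug.

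**The concern.** PGIC asks patients how much they have changed, so the comparison between arms is fair only if every arm answers on the same occasions and under the same conditions. The PGIC section instead ties the answer to an event that two of the three arms undergo and the third does not. In those two arms, it places the answer just after a blade has been inserted at 12 to 20 neck sites, to tendon or ligament level. Soreness or short-lived relief at that moment could colour the rating, and NSAIDs patients rating at an ordinary visit would have no counterpart to it.

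The same sentence also disagrees with the visit table on which weeks carry PGIC. The pilot is meant to supply an effect size and a working protocol for a full-scale trial, so an unclear rule for a named outcome could be carried forward.

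**Working it through.** No statistical formula applies. The check compares sets of visit weeks and then looks at each arm.

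**Step 1. Weeks implied by each statement**

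| Source in the protocol article | Weeks |
|---|---|
| MA sessions, Table 1 | {0, 1, 2} |
| NSAIDs prescriptions, Table 1 | {0, 1, 2} |
| PGIC by the PGIC section (end of each session) | {0, 1, 2} |
| PGIC by Table 1 | {1, 2, 3, 7} |
| PGIC by the Outcomes text | {0, 1, 2, 3, 7} |

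**Step 2. Agreement**

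- PGIC section and Table 1 share {1, 2}, which is 2 of the 4 tabulated PGIC visits.
- The PGIC section alone adds {0}. No treatment has yet had time to act at that visit, and a change scale has nothing to compare with.
- Table 1 alone has {3, 7}, where no session takes place.
- The Outcomes text and Table 1 differ at {0}.

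**Step 3. Do looser readings of a session repair it?**

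- Any treatment visit, with dispensing counted: {0, 1, 2} in all arms. Weeks 0, 3 and 7 still disagree with Table 1.
- Each week of treatment, rated at its end: {1, 2, 3}. Week 7 still does not fit, and the article does not use the word in this sense.

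No reading gives {1, 2, 3, 7}.

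**Step 4. By arm, at the visits where the rule and Table 1 coincide (weeks 1 and 2)**

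The Design section plans 12 patients per arm.

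| Arm | Planned n | Event to which the rule attaches PGIC |
|---|---|---|
| MA | 12 | needling at that visit |
| Combined | 12 | needling at that visit |
| NSAIDs | 12 | none; prescription only |

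Rated directly after needling: 12 + 12 = 24 of 36. Not so rated: 36 − 24 = 12.

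**Step 5. Visits outside the problem**

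Table 1 has no MA session at week 3 or week 7. On that schedule, a PGIC or VAS at either visit follows no needling that day in any arm.

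**The case against.** The strongest reply is that this is one loosely worded sentence and that the rest of the article settles the schedule. Much of that stands, and it limits four stronger inferences that a reader might draw.

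- **That PGIC at weeks 3 and 7 will be lost.** Read in isolation, the PGIC section gives no rating at either week. But the Abstract, the Outcomes text and Table 1 all schedule PGIC there, and the Outcomes section points to the table as the governing schedule: "Table 1 shows the treatment and outcome measurement schedules". Staff would have to disregard all three places, so the loss is unlikely.
- **That PGIC is distorted throughout, or that the primary result is touched.** It is not, on the Table 1 schedule. Any effect of rating after needling is confined to weeks 1 and 2. The primary outcome is the week-3 change in VAS, at a visit without MA.
- **That the NSAIDs arm has no PGIC timing at all.** Table 1 gives one PGIC row for everyone, and NSAIDs patients attend the same visits. What fails in that arm is the session rule, not the visit schedule.
- **That the VAS has the same fault.** The article says that "the VAS score will indicate pain at the point of measurement" and does not place it before or after needling. That is a detail which a journal article may leave to the full protocol, so it is no finding. PGIC differs because the article does state an order for it, and that order cannot be the same in all arms.

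It is also fair to say that the article offers no figure for the size or direction of an immediate procedural effect, so none can be claimed. Two things remain after these concessions: a timing rule that no reading reconciles with the table, and a stated measurement condition at two visits that depends on the arm.

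**Conclusion.** The point holds in a limited form. The PGIC rule contradicts Table 1 and the Outcomes text and does not fit the NSAIDs arm. If it is followed at weeks 1 and 2, 24 of the 36 planned patients rate change directly after needling and 12 do not, so the between-arm PGIC comparison at those two visits cannot separate treatment effect from immediate procedural effect. The direction is unknown and the size is not estimable from the article.

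This rests on two assumptions: that a session means an MA session, as in the Abstract, and that assessors follow the PGIC sentence for the order within a visit. The count of 24 against 12 uses the planned arm sizes.

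Because PGIC is secondary and the week-3 and week-7 comparisons are untouched on the tabulated schedule, this should be corrected but does not threaten the main result. It is more than a slip of wording, because the sentence fixes a measurement condition that differs by arm.

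**What to change.** Replace the sentence in the PGIC section with: *PGIC is completed in all three arms at weeks 1, 2, 3 and 7, relative to week 0, before any needling or dispensing at that visit.*

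In the Outcomes text, exempt PGIC from the week-0 measurement so that it agrees with Table 1, which needs no change.

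The cost is two small text edits and one instruction to the outcome assessors. No visit, questionnaire or treatment is added or altered. Under Trial status, recruitment was already under way, so the trial report should also state when PGIC was actually completed relative to needling at weeks 1 and 2.

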### Safety

The safety of this trial will be assessed by the red blood cell count, hemoglobin level, hematocrit, total white blood cell count, differential count, erythrocyte sedimentation rate, platelet count, aspartate aminotransferase level, alanine aminotransferase level, blood urea nitrogen level, prothrombin time, partial thromboplastin time, C-reactive protein and creatinine levels, serum sodium level, serum potassium level, and serum chloride level. All participants will undergo blood tests twice during the study, once at screening and once at the fourth follow-up visit. Nexina (potassium bismuth citrate 100 mg/Tab, ranitidine hydrochloride 84 mg/Tab, sucralfate hydrate 300 mg/Tab) will be prescribed if the participants complain of dyspepsia symptoms such as nausea, abdominal discomfort, and diarrhea.

All adverse events (AEs) and vital signs will be observed at every visit. Serious AEs (SAEs) will be reported to the IRB. The individuals will be asked to voluntarily report information about AEs and the researchers will confirm the occurrence of AEs through methods such as medical interviews. Details about AEs, such as the date of occurrence, degree of severity, causal relationship with the treatment, other treatments or medications that are suspected to cause the AE, and treatment of the AE, will be reported in detail.

### Withdrawal and dropout

All participants will have the right to withdraw from the study at any time. Participation will be terminated at any stage if the individual refuses to continue, withdraws consent, or violates the inclusion or exclusion criteria. The trial will be stopped if the principal investigator believes that there are unacceptable risks of SAEs.

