## Methods/Design

### Design

The protocol of this assessor-blinded RCT follows the Declaration of Helsinki and Korean Good Clinical Practice. The study will be conducted at Daegu Oriental Hospital of Daegu Haany University, Daegu, Republic of Korea. Independent researchers blinded to randomization will assess the outcomes and analyze statistics. Informed consent to participate in the clinical trial will be obtained after the researcher provides sufficient information and explanations regarding the study interventions. This protocol follows the SPIRIT guidelines and the checklist and figure are available at the end of the manuscript.

This study is designed as a pilot trial to calculate the appropriate sample size for further RCTs. Each group will include 12 participants, allowing for a 20% dropout rate for evaluating the pragmatic purpose of this trial. A total number of 36 participants will be included, which is larger than the minimum number recommended for pilot studies (Additional files 1 and 2).

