### Eligibility criteria

Individuals aged 19–75 years who agree to participate after providing written informed consent will be selected as study volunteers. The inclusion criteria are as follows: men or women aged 19–75 years; symptoms such as neck pain and stiffness lasting for ≥ three months; a baseline score of ≥ 4 on the visual analog scale (VAS) for pain; and provision of written informed consent.

Exclusion criteria are as follows: individuals with abnormalities in neurological functions such as cervical nerve function, deep tendon reflexes, and muscle and sensory functions; those with serious sensory or motor disorders requiring surgical treatment; those with a history of spinal surgery or those with procedures scheduled during the study; those with spinal disorders, including vertebral fracture, spinal infection, inflammatory spondylitis, and malignancy, on computed tomography or magnetic resonance imaging; those who are pregnant, planning pregnancy, breast feeding, or refusing to consume certain forms of contraceptives; those with other chronic diseases that can affect the outcomes of the study interventions, including cardiovascular disease, diabetic neuropathy, active hepatitis, fibromyalgia, rheumatoid arthritis, dementia, and epilepsy; those with other severe musculoskeletal problems in areas other than the neck; those with serious psychiatric or psychological disorders; those using aspirin or anticoagulant medications; those using NSAIDs; those with abnormal findings in blood tests for renal or hepatic function; and those deemed ineligible by the recruiting researcher.

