### Interventions

The MA group will receive MA three times over three weeks. The NSAIDs group will be prescribed zaltoprofen 80 mg/Tab (Soleton, CJ Health Care Co., Ltd, Seoul, Republic of Korea) at a dose of one tablet administered orally three times per day over three weeks. The combined treatment group will receive MA and Soleton over three weeks. The prescription will be administered in every visit and drugs that have not been taken will be withdrawn. During the study period, all other interventions such as moxibustion and physical therapy, surgical procedures, and injections for neck pain will be prohibited. Other medications that do not influence neck pain will be allowed. Any change will be recorded at every visit.

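### The withdrawal rule does not separate late-found ineligibility, stopping treatment and stopping follow-up, so week-3 outcomes could be lost for reasons linked to pain and arm

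*Protocol article*

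**What the plan says.** All references are to the protocol article.

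- **Withdrawal and dropout:** "Participation will be terminated at any stage if the individual refuses to continue, withdraws consent, or violates the inclusion or exclusion criteria". The section does not mention outcome assessment after termination.
- **Eligibility criteria:** the exclusions include "those using aspirin or anticoagulant medications; those using NSAIDs". No period is attached. By contrast, the VAS inclusion threshold is explicitly a baseline score.
- **Interventions:** for MA alone, "The MA group will receive MA three times over three weeks"; for the combination, "The combined treatment group will receive MA and Soleton over three weeks". The NSAIDs arm takes the same zaltoprofen regimen. On concomitant drugs, "Other medications that do not influence neck pain will be allowed", and changes are to be recorded at each visit. No consequence is attached to taking a medicine that is not allowed.
- **Outcomes:** "Changes in VAS scores after three weeks of treatment will be measured relative to the baseline scores and will be considered the primary outcome". Table 1 schedules the VAS at screening and at weeks 0, 1, 2, 3 and 7.
- **Design:** "Each group will include 12 participants, allowing for a 20% dropout rate for evaluating the pragmatic purpose of this trial".

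**The concern.** One sentence covers three different situations: a patient found to have been ineligible at entry, a patient whose study treatment should stop, and a patient whose follow-up should stop. It gives all three the same consequence, the end of participation. One of the exclusion criteria, use of an NSAID or aspirin, can arise after randomisation because pain is not controlled. If the rule is applied to that event, the patient leaves before week 3 and has no primary outcome.

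Such a loss could depend on both pain and arm. Zaltoprofen is assigned treatment in two arms, so on any workable reading the NSAID criterion bears mainly on MA alone. The comparisons exposed are MA with NSAIDs and the combination with MA. The pilot is also meant to supply the effect size and sample size for a full trial, so a distorted arm mean would carry forward. An analysis plan can choose analysis sets and missing-data methods, but it cannot recover a measurement that was never taken.

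**Working it through.** **1. The plan's own figure.** 3 × 12 = 36, which agrees with "A total number of 36 participants will be included". With 20% dropout, 12 × 0.8 = 9.6 per arm remain. In reverse, 9 / 0.8 = 11.25, which rounds up to 12. The article gives no SD, effect size or power, so nothing more can be checked, and the point does not depend on it.

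**2. The sections side by side.**

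| Question | Eligibility criteria | Interventions | Withdrawal and dropout |
|---|---|---|---|
| Is NSAID use disallowed? | Yes, no time limit | Assigned in two arms; otherwise only drugs not affecting neck pain | Any criterion violated |
| When does it apply? | Not stated | During the study | At any stage |
| What follows? | Not selected | Change is recorded | Participation ends |
| Outcomes afterwards? | – | – | Not provided for |

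Taken literally, the first and last columns end participation for everyone in the NSAIDs and combined arms, 24 of 36 patients. That cannot be intended, so some narrower reading must be, and the text does not say which. Renal and hepatic blood tests raise the same question: abnormal findings are an exclusion, and Table 1 repeats laboratory tests at week 3, before the week-7 assessment.

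**3. Size if the rule is applied after randomisation.** Assumptions, none taken from the documents:
- k of the 12 MA-alone patients are removed, and nobody from the comparison arm.
- The patients removed are those ranked worst on a pain score that has correlation ρ with the week-3 VAS change.
- Both variables are normal.

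Shift in the MA-alone mean, in SD units, in its favour:

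shift = ρ × S_k / (12 − k),

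where S_k is the sum of the k largest expected order statistics of 12 standard normal values (1.629, 1.116, 0.793).

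| k | S_k | S_k / (12 − k) | ρ = 0.3 | ρ = 0.5 | ρ = 0.7 | ρ = 1.0 |
|---|---|---|---|---|---|---|
| 1 | 1.629 | 1.629 / 11 = 0.148 | 0.044 | 0.074 | 0.104 | 0.148 |
| 2 | 2.745 | 2.745 / 10 = 0.274 | 0.082 | 0.137 | 0.192 | 0.274 |
| 3 | 3.538 | 3.538 / 9 = 0.393 | 0.118 | 0.197 | 0.275 | 0.393 |

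At ρ = 0 the shift is 0 for every k. Simulation with 100,000 replicates agrees to within about 0.001.

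**4. In centimetres.** For k = 2 and ρ = 0.7, with an assumed SD of 1.5 to 2.5 cm: 0.192 × 1.5 = 0.29 cm to 0.192 × 2.5 = 0.48 cm.

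**5. Effect on a test.** With equal true means, a complete-case t-test at two-sided 0.05 and one-sided removal, the simulated type I error for k = 1, 2, 3 at ρ = 0.7 is 0.060, 0.077 and 0.103, mostly in favour of MA alone.

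**6. Removal in both arms.** If the comparison arm also loses its worst patients, the shifts partly cancel. With 2 removed from MA alone and 1 from the comparator at ρ = 0.7, the net shift is 0.192 − 0.104 = 0.088 SD.

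**The case against.** The strongest reply is that the eligibility list describes who is selected, so NSAID use is an entry criterion and the withdrawal rule covers ineligibility that is discovered late. On-study medication has its own section, which records changes and attaches no termination to them. This is a fair reading, and it is why the point is a conflict to reconcile. A reader might infer that the plan definitely removes MA-alone patients who take an NSAID and so flatters that arm. The documents do not establish that. Equally, the withdrawal sentence applies at any stage and the NSAID criterion is not tied to baseline, so the text does not exclude it.

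A reader might also infer that all data from such patients are lost. No section says that visits already made are discarded. What is missing is any provision for later ones. Nor can it be said that the rule adds to the 20% dropout, because that allowance may already include these terminations.

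The direction is conditional. An NSAID-arm patient who adds aspirin or another NSAID would meet the same rule, and the documents give no rate of such use. In a 36-patient pilot with a preliminary report, a shift of this size is modest beside the sampling error of 12 per arm.

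Keeping the patients also has a price. The VAS records pain at the moment of measurement, so a week-3 value taken after an NSAID may include relief from it and can itself favour MA alone.

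One reply fails: that an analysis plan or the full protocol's analysis detail would settle the matter. The point concerns a rule that the article states, and analysis rules cannot replace values never collected.

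**Conclusion.** The point holds as an ambiguity with a conditional bias. The article states a termination rule that makes no distinction between entry ineligibility, stopping treatment and stopping follow-up, and it conflicts with the assigned treatment of two arms if read literally. Applied after randomisation, it can cost a randomised patient every outcome from that point, including the primary one.

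If the loss is driven by worse pain and concentrated in MA alone, it favours that arm by 0.104 to 0.275 SD for 1 to 3 of 12 removed at ρ = 0.7, and by about 0.04 to 0.39 SD over ρ from 0.3 to 1.0. It is zero if removal is unrelated to outcome and smaller if both arms lose such patients. The number removed, ρ, the SD and the one-sided removal are all assumptions. The change is worth making because it is cheap and the loss cannot be repaired later.

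**What to change.** Reconcile Eligibility criteria, Interventions and Withdrawal and dropout, stating which criteria apply at entry only and which continue after randomisation.

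In Withdrawal and dropout, end outcome collection only when the patient withdraws consent to follow-up. For any other violation or stopped treatment:
- record the event and its date;
- keep the scheduled assessments to week 7;
- analyse the patient in the randomised arm;
- report analgesic use by arm.

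Add a sensitivity analysis for week-3 values obtained after off-protocol analgesic use, and say in the report that such relief may favour MA alone.

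The cost is a few sentences, one sensitivity analysis, and visits that are already in Table 1. The downside is that some retained values answer a slightly different question, MA with whatever analgesic was taken. This concerns data collection only; no treatment, rescue or stopping rule is proposed.
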